#### Monitoring

Monitoring according to GCP/ICH will be performed by trained personnel allocated by the sponsor, The Public Health Agency of Sweden.

#### Ethical issues

It is important to include children in clinical trials, especially since children often suffer from infections and therefore are treated with antibiotics more often than other age groups. The lower age limit 6 years was chosen based on presumed ability to swallow tablets, since exposure is easier to control with tablets than with oral suspension.

We consider that there are no risks to participate in the study, regardless of age. The sampling is simple and follow the normal routines at the PHCCs. Both treatment alternatives are expected to be effective against the infection. A shorter treatment regimen could include benefits in form of less adverse events and less disturbances in the human microbiota. In addition, patient adherence to the treatment may improve with shorter treatment duration.

## Discussion

In the era of increasing antimicrobial resistance and the shortage of new antimicrobial agents it is necessary to revisit old antibiotics to ensure that they are used correctly and to their full potential. Important old drugs deserve to be rigorously tested according to today’s standards and requirements for clinical studies. Old antimicrobial drugs are often associated with inadequate knowledge on PK/PD and lack of optimized dosing regimens based on randomized controlled clinical trials.

Since old antibiotics are usually out of patent protection, financial incentives to perform the necessary studies are lacking. Thus, public funding is often the only option available [16]. For the current study, funded by the Swedish government, an initial systematic review to identify knowledge gaps was performed, followed by a structured prioritizing process by independent experts, in order to select the most needed non-clinical and clinical studies.

There is currently no substantial scientific evidence to recommend less than 10 days treatment of penicillin V against streptococcal pharyngotonsillitis. A shorter treatment period though, with lower total antibiotic exposure, is expected to reduce the risk of ecological disturbance on the human microbiota [17] and possibly improve patient adherence [13].

One possible disadvantage with a shorter treatment duration could be an increased risk for relapses, since the time with protection against a new infection is shorter. Furthermore, it could be argued that the daily dose for the 5-day treatment is slightly higher than the recommended daily dose, which may increase the risk for adverse events. However, there is extensive clinical experience of even higher doses in treatment of other infections like acute otitis media, sinusitis, and dental infection, justifying the safety profile of penicillin V also at high doses.

Overall we believe that this study, facilitated by public funding, may contribute with important knowledge and may have a substantial impact on public health. If a shorter and more potent treatment regimen is shown to be equivalent with the normal 10 day regimen this can imply great advantages for both patients (resistance, adverse events, adherence) and the community (resistance, drug costs).

## Abbreviations

CRF: Case record form
GAS: Gtreptococcus group A
GCP: Good clinical practice
ICH: International conference on harmonization
MIC: Minimum inhibitory concentration
MITT: Modified intention to treat population. Patients who received at least one dose of the study drug
PHC: Primary health care
PHCC: Primary health care centre
PK/PD: Pharmacokinetics and pharmacodynamics
PP: Per protocol population. Patients without violations to the study protocol, receiving at least 80 % of the prescribed study drug and evaluable at least until the TOC visit.
RADT: Rapid antigen detection test
RCT: Randomized controlled trial
TOC: Test of cure

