### Design

This Phase IV study is a randomized, open-label, multicenter study with non-inferiority design regarding the therapeutic use of penicillin V with two parallel groups.

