#### Visit one

Patients presenting with sore throat will be clinically examined by a physician. In case of suspected faryngotonsillitis and 3–4 Centor criteria a RADT for GAS will be performed. Patients with a positive RADT test for GAS who meet all the inclusion criteria, and none of the exclusion criteria, will be asked to participate in the trial. After signed informed consent, by patient or guardian, the patient will be asked about medical history, demographic data, previous antibiotic exposure and concomitant drug treatment.

A throat swab for semi quantitative cultures of streptococcus group A, C and G will be performed.

After randomization to intervention group 5 or 10 days the physician prescribes penicillin V which the patient will retrieve from the pharmacy. A patient diary is handed out which the patient or guardian is asked to fill in until the follow-up visit, five to seven days after treatment discontinuation.

Demographic data and clinical data will be recorded in a case report form (CRF) by study personnel. In addition, data regarding intake of penicillin V doses and analgesics, presence of sore throat and fever, adverse events etc. is filled in daily by each patient or guardian in the diary.

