#### Follow-up controls

Follow-up controls will be done by a telephone call 1 month (28–35 days) and 3 months after the last treatment day. Throat symptoms, potential relapses and complications will be monitored as well as adverse events ongoing at previous visits.

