### Definitions

Definitions of outcome measures are presented in Table 3.

**Table 3 Tab3:** Definitions of outcome measures

Term	Definition
Clinical cure	Clinical judgement by physician 5–7 days after discontinuation of treatment. Patient completely recovered with no remaining/residual symptoms or clinical findings of pharyngotonsillitis or symptomatic relapse at TOC.
Therapeutic failure	None or inadequate clinical effect during treatment period.
Not evaluable for primary outcome	Follow-up after discontinuation of treatment is missing.
Relapse	Symptomatic pharyngotonsillitis within one month after first diagnosis, according to clinical judgement by physician 1) antibiotic treatment necessary or 2) verified pharyngotonsillitis caused by streptococcus. Recurrent symptomatic pharyngotonsillitis presenting before and including the TOC visit, following at least 1 day without symptoms after initial treatment, will be judged as early relapse.
Complication with suspected relation to the primary infection	For example peritonsillitis, acute otitis media or sinusitis during the study period, i.e. until the last follow-up visit.
Bacteriological cure	Absence of GAS in culture. If culture is missing, a negative RADT.
Asymptomatic carriage of GAS	Presence of GAS in culture from patient *without* throat symptoms. If culture is missing, a positive RADT.
Symptomatic infection of GAS	Presence of GAS in culture from patient *with* throat symptoms. If culture is missing, a positive RADT.

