### Statistical analysis

#### Sample size/power calculation

The power calculation is based on the assumption of 90 % clinical recovery in the reference group and no difference between the two groups. The non-inferiority limit is set to minus 10%, the confidence level (two-sided) to 95 %, the power to 85 % and the distribution between the groups to 1/1. Based on these presumptions, 324 evaluable patients (162 in each group) are needed to be able to demonstrate non-inferiority between treatment groups. Presuming that 25 % of the included patients will not be possible to evaluate 432 (324*(1/0.75)) patients are needed to be included.

All effect variables will be analyzed for per protocol population (PP) as well as for the modified intention to treat (MITT) population as sensitivity analysis.

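### The MITT sensitivity set shares with PP the loss of never-dosed patients and, as Table 3 is worded, of patients without follow-up, so it checks the PP result only in part

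*Protocol article*

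**What the plan says.** The trial is a "randomized, open-label, multicenter study with non-inferiority design" (Design). The statistical section names two analysis sets: PP, "as well as for the modified intention to treat (MITT) population as sensitivity analysis" (Sample size/power calculation). Both are defined under Abbreviations:

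- **MITT:** "Patients who received at least one dose of the study drug".
- **PP:** no protocol violation, at least 80% of the prescribed drug taken, and evaluable up to the TOC visit.

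Under Visit one the order of events is: "After randomization to intervention group 5 or 10 days the physician prescribes penicillin V which the patient will retrieve from the pharmacy". First intake therefore comes after the arm is known.

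Table 3 (Definitions) has a category for patients who cannot be evaluated for the primary outcome, described as "Follow-up after discontinuation of treatment is missing". It is not limited to PP, and the article gives no failure or imputation rule for these patients.

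The sample size assumes that 25% "of the included patients will not be possible to evaluate", without dividing that share by cause. No analysis of all randomised patients as allocated is described.

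**The concern.** In an open-label non-inferiority trial with PP as the main analysis, the companion analysis should show whether post-randomisation exclusions drive the result. It does so only for exclusions that it reverses. Two are not reversed here.

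1. **Never dosed.** Non-starters are absent from both sets. Because patients know their arm before they collect the drug, not starting can depend on the arm.
2. **No follow-up.** PP requires evaluability up to TOC. MITT does not, but under Table 3 a dosed patient without follow-up has no primary outcome to contribute. Attendance may differ by arm: TOC is 5–7 days after the end of treatment, so it falls 5 + 5 to 5 + 7 = 10–12 days after the start in one arm and 10 + 5 to 10 + 7 = 15–17 days in the other.

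If patients who do badly on the short course are lost more often than those on the long course, PP and MITT could agree with each other and both be too favourable to the 5-day regimen. The Discussion itself names a higher relapse risk as a possible drawback of the shorter course.

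**Working it through.** **1. The plan's own figure.** Inputs from Sample size/power calculation: cure 90% in both arms, margin 10 points, two-sided 95% confidence, power 85%, allocation 1:1.

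n per arm = 2 × 0.90 × 0.10 × (1.960 + 1.036)² / 0.10² = 0.18 × 8.978 / 0.01 = 161.6, so 162 per arm and 324 in all. Then 324 / 0.75 = 432. All three figures reproduce; the sample size is not in question.

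**2. What MITT adds to PP.** The expected non-evaluable number is 432 − 324 = 108. How many of these are never dosed or without follow-up is not stated, so a range is needed:

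| Share of the 108 that is never dosed or without follow-up | MITT patients with an outcome | More than PP |
|---|---|---|
| 100% | 324 | 0 |
| 75% | 351 | 27 |
| 50% | 378 | 54 |
| 25% | 405 | 81 |
| 0% | 432 | 108 |

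**3. Result among those seen, at the upper bound.** With 162 per arm and 90% cure in both, the standard error is √(2 × 0.09 / 162) = 3.33 points and the half-width is 1.96 × 3.33 = 6.5 points. The lower limit is −6.5, so non-inferiority is shown.

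**4. Result over all 216 per arm, with 54 unseen in each.** Assume 90% cure among everyone seen and among unseen 10-day patients, and cure q among unseen 5-day patients. Overall 5-day cure is p = 0.75 × 0.90 + 0.25 × q. The lower limit is (p − 0.90) − 1.96 × √[(p(1 − p) + 0.09) / 216].

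| q | p | Difference (points) | Lower 95% limit (points) |
|---|---|---|---|
| 80% | 0.875 | −2.5 | −8.5 |
| 74% | 0.860 | −4.0 | −10.1 |
| 70% | 0.850 | −5.0 | −11.2 |

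The limit meets −10 at p = 0.861, a fall of 3.9 points. That is 0.039 × 216 ≈ 8.4 additional failures, about 8–9 of the 54 unseen 5-day patients.

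**5. Fewer unseen.** The same 3.9-point fall has to come from a smaller group. With a share m unseen in each arm, q = 0.90 − 0.0389 / m:

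- m = 25%: q ≈ 74%
- m = 10%: q ≈ 51%
- m = 5%: q ≈ 12%

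Each is set against 90% in unseen 10-day patients. The conclusion is fragile near the upper bound and robust when few patients are unseen.

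**6. Counting every missing patient as a failure.** At 25% missing in both arms, cure is 0.75 × 0.90 = 0.675. The standard error is √(2 × 0.675 × 0.325 / 216) = 4.51 points and power is Φ(10 / 4.51 − 1.96) = Φ(0.26) ≈ 60%. At 10% missing, power is 75%. That rule is therefore a costly way to fill the gap.

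**The case against.** A reader might infer that MITT merely repeats the PP exclusions and so cannot check PP at all. The definitions do not support this. MITT brings back dosed patients with protocol violations or with less than 80% of the drug. The arms differ in duration and daily frequency, and the article expects adherence to differ, so those exclusions are worth checking and MITT does check them.

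A reader might also infer that MITT by definition drops everyone without a TOC visit. It does not: the evaluability condition is written into PP and left out of MITT. The second limb arises only when MITT is read together with Table 3, which defines outcomes and not populations. Table 3 also has separate entries for therapeutic failure during treatment and for early relapse, so a patient who fails early and then misses TOC may be classifiable, although the table does not say which entry takes precedence. A rule for missing outcomes may stand in the full protocol or the SAP, neither of which is shown, and its absence from the article is not an error.

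Two further objections hold. The number of non-starters is given nowhere, and both arms get the same drug by the same route, so arm-related non-starting is possible but unquantified. A one-dose set used as a sensitivity analysis is also a common choice.

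What remains is in the stated text: both named sets leave out never-dosed patients after an open allocation, none keeps all randomised patients, and Table 3's wording gives patients without follow-up no primary outcome in either.

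**Conclusion.** The point holds as a limitation of the sensitivity analysis. MITT tests PP's adherence and violation exclusions but cannot show bias from arm-related non-starting or, as Table 3 is worded, from missing follow-up. Agreement between PP and MITT would be no reassurance on those two.

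The size is unknown. At most 108 of 432 patients (54 per arm) are concerned, and only if the whole unsplit 25% is non-starting or missing follow-up. In that case cure of about 74% among unseen 5-day patients, against 90% elsewhere, is enough to move the lower limit past the margin. With 10% unseen it takes about 51%. These figures rest on the plan's 90% cure rate, equal numbers unseen in each arm and a normal-approximation interval. They do not show that the trial's result is biased; they show what the two planned analyses would be unable to detect. The change is worth making because it is cheap.

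**What to change.** 1. Define the sensitivity population as all randomised patients, analysed as allocated, whether or not a dose was taken. The one-dose set may be kept beside it.
2. State that Table 3's not-evaluable category does not remove anyone from that analysis. Classify patients without a TOC visit where possible from the daily diary, from recorded failure or relapse, and from the 1-month call, at which "Throat symptoms, potential relapses and complications will be monitored".
3. For those still unknown, report a tipping-point analysis with the assumed cure rate varied separately by arm. This is preferable to counting all of them as failures, given the loss of power shown above.
4. Leave PP as it is.

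Cost: a change of wording in the population definition and Table 3, and one more analysis. No patients or visits are added. The sensitivity interval may be wider or less favourable, and a status taken from diary or telephone is less certain than a physician's judgement at TOC, so the number classified that way should be reported by arm.

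### The main (per-protocol) analysis set has no exception for documented treatment failures or early relapses, so known non-cures can leave it because of their outcome, with a bias of undetermined direction

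*Protocol article*

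**What the plan says.** **Main analysis set.** Under Sample size/power calculation, all effect variables are to be "analyzed for per protocol population (PP) as well as for the modified intention to treat (MITT) population as sensitivity analysis". PP is therefore the main set and MITT the sensitivity set.

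**PP.** The Abbreviations list defines it as "Patients without violations to the study protocol" who received at least 80% "of the prescribed study drug and evaluable at least until the TOC visit". There is no exception for patients whose treatment has already failed.

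**MITT.** "Patients who received at least one dose of the study drug", with no intake or TOC condition.

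**Outcome terms (Definitions, Table 3).** Therapeutic failure is "None or inadequate clinical effect during treatment period". Early relapse may present before the TOC visit as well as at it. A patient is not evaluable for the primary outcome if "Follow-up after discontinuation of treatment is missing". The table does not say that a failure or relapse documented before TOC counts as not cured in PP, and the not-evaluable row does not exempt such patients.

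**The concern.** Table 3 recognises bad outcomes that become known before TOC, but the PP definition does not provide for them. As written:

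- a patient who stops for lack of effect before reaching 80% of the prescribed doses leaves PP;
- a patient with a documented failure or early relapse who has no later assessment can also leave it, through the TOC condition.

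In both cases a known non-cure disappears from numerator and denominator, and it does so because of the outcome. Few such losses are needed to matter: at the planned 90% cure, about 16 non-cures are expected among 162 patients (162 × 0.10 = 16.2).

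The intake rule also treats the arms differently, because 80% of a 5-day course is complete four days before 80% of a 10-day course. The trial is open-label, so knowledge of the arm may influence who stops. At stake are the error rate and the power of the main non-inferiority conclusion.

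**Working it through.** **1. The plan's own figure.** Inputs from Sample size/power calculation: 90% cure in both arms, margin 10 points, two-sided 95% confidence, 85% power, 1:1 allocation.

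n per arm = (1.960 + 1.036)² × (2 × 0.90 × 0.10) / 0.10² = 161.6, so 162 per arm and 324 evaluable. Then 324 / 0.75 = 432. All three figures reproduce, and the sample size is not in error.

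**2. When the intake threshold is reached.** Regimens from Intervention, Table 1.

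- 5-day arm: 4 × 5 = 20 doses; 80% = 16 doses; 16 / 4 = day 4.
- 10-day arm: 3 × 10 = 30 doses; 80% = 24 doses; 24 / 3 = day 8.

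A patient who actually stops the drug between these two points meets the intake rule in the 5-day arm but not in the 10-day arm.

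**3. Effect on the apparent cure rate.** If true cure is p and a share f of the non-cures is removed, apparent cure = p / (1 − f(1 − p)). Example with f = 0.20: 0.80 / 0.96 = 0.833 and 0.90 / 0.98 = 0.918, so a true difference of −10.0 points appears as −8.5.

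**4. Chance of declaring non-inferiority when the 5-day regimen is exactly at the margin.** True cure is 90% (10-day) and 80% (5-day), with 162 patients per arm in the analysed set. The probability that the lower 95% Wald limit lies above −10 points is summed exactly over the two binomial distributions. The shares f are assumptions; the documents give none.

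| Share of non-cures removed (10-day / 5-day) | Apparent difference (points) | False non-inferiority |
|---|---|---|
| 0 / 0 | −10.0 | 2.7% |
| 5% / 5% | −9.6 | 3.3% |
| 10% / 10% | −9.3 | 4.1% |
| 20% / 20% | −8.5 | 6.5% |
| 30% / 30% | −7.7 | 10.4% |
| 50% / 50% | −5.8 | 29% |
| 10% / 5% | −10.1 | 2.5% |
| 20% / 10% | −10.2 | 2.4% |
| 40% / 20% | −10.4 | 2.1% |
| 50% / 25% | −10.5 | 2.0% |
| 0 / 25% | −5.8 | 21% |
| 20% / 0 | −11.8 | 0.8% |
| 30% / 0 | −12.8 | 0.4% |

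Taking 162 per arm before removal instead changes little: 10.5% rather than 10.4% for 30% / 30%, and 27% rather than 29% for 50% / 50%.

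**5. Power when the regimens are truly equal.** True cure is 90% in both arms and non-cures are removed only from the 10-day arm. Apparent control cure becomes 0.90 / 0.98 = 0.918 (20%) or 0.90 / 0.97 = 0.928 (30%). Power falls from about 85% to about 72% or 64%.

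**6. Direction.** The intake rule alone has the longer reach in the 10-day arm, so it may remove more failures there, which works against the 5-day regimen. The TOC condition could act the other way if 5-day patients relapse after treatment and are not assessed at TOC; the Discussion itself names relapse as a possible disadvantage of shorter treatment. The documents give no rates from which to tell which effect is larger.

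**The case against.** **The stronger reading.** A reader might infer that these rules make it likely that an inferior regimen passes as non-inferior. The documents do not support that. Inflation requires roughly equal loss in both arms, or more loss in the 5-day arm. The later threshold in the 10-day arm points, for the intake rule, to the opposite pattern; with twice the share lost there, the false-claim rate stays at or below its nominal level and the cost is power. This part of the objection stands, and the point is therefore stated without a direction.

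**Table 3.** A reader might also take the not-evaluable row to cover every known failure who misses TOC. The row is narrower: it concerns missing follow-up after treatment ends. A patient who fails, stops and is seen again has such follow-up. What remains is that the PP wording leaves this patient's status unclear and the row exempts nobody.

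**Reach of the intake rule.** It removes a failing patient only if the drug is actually stopped before dose 16 or dose 24. Patients who finish and still have symptoms or findings at TOC stay in PP as not cured. This also stands, and it limits the plausible shares.

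**MITT.** All effect variables are analysed there too, "as well as for the modified intention to treat (MITT) population as sensitivity analysis", and early stoppers who are followed remain in it, so a discrepancy would be visible. But the article does not require the two sets to agree, and the not-evaluable row does not exempt documented failures in MITT either.

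**Condensed article.** A full protocol or analysis plan, not shown, may carry failures forward. The point does not rest on that silence. It rests on the inclusion rule the article does state, which such a provision would have to change.

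**Conclusion.** The point holds as a defect in a stated definition. The PP set, which carries the main result, can lose known non-cures because of their outcome, and its intake threshold falls on day 4 in one arm and day 8 in the other.

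The size depends on assumed loss. Equal loss of 5–30% takes the false non-inferiority rate from 2.7% to 3.3–10.4%. Twice the loss in the 10-day arm leaves it near 2.0–2.4% (2.5% at the smallest shares). Loss of 20–30% in the 10-day arm only, with equal true cure, costs roughly 13 to 21 points of power (85% to about 72% or 64%).

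No direction of bias can be claimed from the documents. The figures also assume that only non-cures are removed and that a 95% Wald limit is used. The MITT analysis mitigates the problem without removing it.

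**What to change.** 1. Amend the PP definition so that a patient with a documented therapeutic failure, an early relapse or a new antibiotic for pharyngotonsillitis before TOC is kept and counted as not cured, whatever the intake or TOC attendance.
2. Apply the 80% intake rule and the TOC rule only to patients without such an event.
3. Limit the not-evaluable row of Table 3 to patients without a prior documented failure or relapse.

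This changes how outcomes are classified for analysis, not how patients are treated. With every known failure kept (f = 0 in both arms), the false non-inferiority rate at 90% versus 80% returns to 2.7%. The cost is the wording of one population definition and one table row. Observed cure rates may be slightly lower. No new data are needed, and 162 per arm, 324 evaluable and 432 included stay as planned.
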